#### Frozen embryo transfer after thawing

Patients were given 4 mg of exogenous estrogen on the 2nd/3rd day of menstruation at a maximum dose of 8 mg for a total of 15–20 days. When the endometrial thickness was ≥7 mm, progesterone was given for endometrial transformation, and embryo transfer was generally performed on days 20–22. Three-dimensional ultrasonography was performed to evaluate the endometrial thickness and morphology, intrauterine volume, endometrial VFI, FI, VI, and uterine artery blood flow resistance. Between 1 and 2 high-quality embryos were transplanted. Blood beta (β)-hCG and progesterone were measured 14 days after embryo transplantation. At 35 days after embryo transfer, B-scan ultrasonography was performed to check the clinical pregnancy status.

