### Secondary outcome measures

These included the endometrial thickness, menstrual volume, and clinical pregnancy rate.“Endometrial thickness” referred to the anterior and posterior diameter of the endometrium in the longitudinal section of the uterus, which changed with the menstrual cycle. The measurement of endometrial thickness was based on the following: In the median sagittal section of the uterine body, perpendicular to the midline of the endometrium, the maximum thickness diameter was measured between the lateral edges of the double-layer endometrium. If there was uterine effusion, the thickness and diameter of the two monolayers were measured and added to the overall total.The evaluation of menstrual volume is the total amount of bleeding in each menstrual cycle. The normal menstrual volume is 20–60 ml, and more than 80 ml is considered to be excessive. Typically, this is judged by the number of sanitary napkins used. Under normal circumstances, 10–20 sanitary napkins will be used in a menstrual cycle. If the level of menstruation required fewer than 10 sanitary napkins or only one was needed, the amount of menstruation had been reduced. Based on the number of sanitary napkins that were used before the hysteroscopy, if this was more than the amount before the procedure, the amount of menstruation was considered to have increased. If there was no change in the menstrual volume compared with before the procedure, the menstrual volume was considered as having shown no improvement.Blood β-hCG and progesterone were measured 14 days after embryo transfer to evaluate whether a biochemical pregnancy was present. On day 35 after embryo transfer, a vaginal ultrasound showed that there was a gestational sac in the uterus with an embryo and fetal heart beat; this was determined as a clinical pregnancy.Ongoing pregnancy rate = the number of clinical pregnancies ≥12 weeks/the number of embryo transfer cycles × 100%Clinical pregnancy rate = the number of clinical pregnancies/the number of embryo transfer cycles × 100%Embryo implantation rate = the total number of implanted embryos/the total number of transplanted embryos × 100%Ectopic pregnancy rate = the number of ectopic pregnancies/the total number of clinical pregnancies × 100%Early spontaneous abortion rate = the number of spontaneous abortions at a gestational age of <12 weeks/the total number of clinical pregnancies × 100%

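### Clinical and ongoing pregnancy rates are divided by embryo transfer cycles, so randomised women who never reach transfer drop out of the comparison, and no rate per randomised woman is defined

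*Protocol article*

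**What the plan says.** Under Secondary outcome measures, the article fixes the denominators itself:

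- "Clinical pregnancy rate = the number of clinical pregnancies/the number of embryo transfer cycles"
- "Ongoing pregnancy rate = the number of clinical pregnancies ≥12 weeks/the number of embryo transfer cycles"
- "Embryo implantation rate = the total number of implanted embryos/the total number of transplanted embryos"

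The same section ties the event to transfer: "On day 35 after embryo transfer, a vaginal ultrasound showed that there was a gestational sac in the uterus", with an embryo and heartbeat, is what makes a clinical pregnancy. No pregnancy rate per randomised woman appears anywhere in the article.

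Four other places bear on this:

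- Randomization and allocation: the envelope is opened during the first hysteroscopy, once adhesions are graded moderate or severe. Hormone therapy, the second-look hysteroscopy and then transfer all come later.
- Frozen embryo transfer after thawing: "When the endometrial thickness was ≥7 mm, progesterone was given for endometrial transformation, and embryo transfer was generally performed on days 20–22". The section does not say what happens below 7 mm.
- The inclusion criteria require a thin endometrium, for which Evaluation criteria cites a usual threshold of under 7 mm. Endometrial thickness is also a listed secondary outcome.
- The withdrawal criteria include becoming pregnant while under treatment. The period meant by treatment is not defined.

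By contrast, the primary response rate is divided by the number of subjects in the group.

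**The concern.** Randomisation makes the groups comparable at the first hysteroscopy. A rate per transfer cycle compares only those who later have a transfer, and having one depends on endometrial thickness, which the scaffold is meant to improve. If the scaffold helps by bringing more women to 7 mm, dividing by transfers removes that part of the benefit. If the additional women brought to transfer have a different prognosis, the per-transfer rates are also no longer like for like.

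Better pregnancy outcome is a stated aim in the Abstract and Background, so this matters although the outcomes are secondary.

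A smaller matter runs alongside. A woman who conceives before any transfer cannot meet a definition that starts from transfer, and may also be withdrawn. Her pregnancy is then not counted in either group.

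**Working it through.** The article states no expected value, power or size for the pregnancy rates, so there is no figure of its own to reproduce. The check sets the definitions side by side and then shows what the denominator can do.

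**Inputs**

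- Pregnancy rate: 22.5% to 33.3%, from the Background, for severe adhesions. Using it as a per-transfer rate is an assumption, because the article does not state its denominator.
- Share of each group reaching transfer: not given. Assumed between 60% and 90%.
- One transfer per woman: assumed, for simplicity.

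**Formula**

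Rate per randomised woman = share reaching transfer × rate per transfer.

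**Case 1: the same per-transfer rate in both groups.** The planned comparison shows a difference of zero in every row. Differences are taken before rounding.

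| Rate per transfer | Share reaching transfer, scaffold vs control | Per randomised woman | Difference (points) |
|---|---|---|---|
| 33.3% | 90% vs 80% | 30.0% vs 26.6% | 3.3 |
| 33.3% | 90% vs 70% | 30.0% vs 23.3% | 6.7 |
| 33.3% | 85% vs 60% | 28.3% vs 20.0% | 8.3 |
| 22.5% | 90% vs 80% | 20.25% vs 18.0% | 2.25 |
| 22.5% | 90% vs 70% | 20.25% vs 15.75% | 4.5 |
| 22.5% | 85% vs 60% | 19.1% vs 13.5% | 5.6 |
| either | 90% vs 90% | equal | 0 |

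**Case 2: the additional women reaching transfer have a poorer prognosis.** Let 90% vs 70% reach transfer. Of the scaffold group, 70% conceive at 33.3% per transfer, as in the control group, and the additional 20% conceive at an assumed 15%.

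- Scaffold, per transfer: (0.70 × 0.333 + 0.20 × 0.15) / 0.90 = 29.2%. Control: 33.3%. Difference −4.1 points.
- Scaffold, per randomised woman: 0.70 × 0.333 + 0.20 × 0.15 = 26.3%. Control: 0.70 × 0.333 = 23.3%. Difference +3.0 points.

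The sign changes with the denominator.

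**Case 3: conceptions before transfer.** Suppose 8 vs 3 of 100 women conceive before transfer (arbitrary numbers), and in both groups 90% of the rest have a transfer at 33.3%.

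- Per transfer: 33.3% in both groups.
- Per randomised woman, all conceptions counted: (92 × 0.9 × 0.333 + 8) / 100 = 35.6% vs (97 × 0.9 × 0.333 + 3) / 100 = 32.1%.
- With 5 in each group the two rates are equal, at 33.5%.

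**The case against.** The strongest reply is that the bias needs unequal transfer shares, and the article gives no reason to expect a particular imbalance. Both groups have the same hormone therapy, second look and estrogen preparation before transfer. With equal shares Case 1 gives zero. This stands as a limit on direction and size. It does not rescue the denominator, because whether the shares differ is part of what the trial would show.

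The differences are also small for this trial. With 100 women per group, the largest (28.3% vs 20.0%) has a standard error of about √(0.283 × 0.717/100 + 0.200 × 0.800/100) = 6.0 points. The issue is which comparison is estimated, not a result that would otherwise be detected reliably.

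A reader might infer more than the text supports:

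- *The control group keeps only its best-prognosis women.* This presumes that the scaffold changes who reaches transfer, which is under test. The text also never says that women below 7 mm have no transfer; it only ties the preceding progesterone step to that threshold.
- *Withdrawal on pregnancy removes the best outcomes from the numerator.* A conception before transfer was never in a numerator defined from transfer, and it is outside the denominator too. Such cases are probably few in women with repeated implantation failure who have IVF/ICSI indications. The article gives no count and does not say that withdrawn women are dropped from analysis.
- *Repeat cycles make the intervals too narrow by a known factor.* Cycles per woman are not capped, but repeat transfers are not described. No within-woman correlation is given, and Statistical analysis methods specifies no interval for rates. Only the transfer of 1–2 embryos is stated, so clustering is a reason for care and not a sized error.
- *The trial's main comparison is compromised.* It is not: the primary response rate uses all subjects in the group.

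**Conclusion.** The point holds for the secondary pregnancy outcomes. As written, clinical and ongoing pregnancy are compared among transfer cycles, and reaching transfer depends on a post-randomisation variable that the scaffold is meant to improve. No rate per randomised woman is defined to set beside them. Because the article fixes these denominators itself, this is not a detail left to an analysis plan.

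Under the assumed shares, equal per-transfer rates could conceal about 2 to 8 points per randomised woman, and a reversal of sign is possible. These sizes rest wholly on the assumed shares, on reading the Background rate as per transfer, and on one transfer per woman. The true direction and size are unknown.

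The uncounted conceptions before transfer are a lesser matter. The withdrawal criterion, with its undefined treatment period, needs to be reconciled with the pregnancy outcome. Read broadly enough to include pregnancy after transfer, it would withdraw the very women whose pregnancies are to be counted.

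**What to change.** Make the main between-group comparison, for clinical and for ongoing pregnancy:

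*women with at least one clinical (ongoing) pregnancy within a fixed, pre-stated follow-up window, divided by all women randomised to that group.*

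With it, state that:

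- women without a transfer count as not pregnant unless they conceive by another route;
- conceptions by any route are followed for outcome and counted, under a definition of clinical pregnancy that does not depend on a transfer date;
- the period meant by treatment in the withdrawal criterion is defined, and withdrawal is reconciled with outcome follow-up. Whether study treatment stops on pregnancy is a clinical matter outside this change.

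Keep the per-transfer and per-embryo rates as supplementary, with woman-level cluster-robust intervals, since 1–2 embryos are transferred and cycles per woman are not capped. Report the number and share of each group reaching transfer beside them.

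No transfer criterion or treatment rule changes. The cost is revised wording plus outcome follow-up of women who have no transfer or who conceive early. The headline rates will be lower than per-transfer rates and less easily set beside published per-transfer figures.

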**Methods:**

This paper presents a prospective randomized single-blind controlled superiority study of infertile women aged ≤40 years with IUA. According to the scoring criteria for IUA established by the American Fertility Society, patients with moderate or severe IUA were randomized into two groups at a ratio of 1:1; patients in the experimental group were treated with an ECM scaffold (small intestinal submucosa [SIS]) + intrauterine balloon, while patients in the control group were treated with an intrauterine balloon only. A hysteroscopic examination of adhesion repair was performed again after 2 months of postoperative hormone replacement therapy. Endometrial tissue was sampled during the two operations, and immunohistochemistry was used to observe endometrial and microvascular proliferation. After thawing and resuscitation, a postoperative frozen embryo transfer was performed on the participants in both groups, and their endometrial thickness, intrauterine volume, endometrial vascularization flow index, endometrial flow index, and uterine artery blood flow resistance were evaluated by 3D ultrasonography. The rates of embryo implantation, clinical pregnancy, and early spontaneous abortion were observed.

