#### Embryo scoring criteria

The criteria for embryo evaluation at the cleavage stage and embryo scoring were as follows:Grade I: Blastomeres that were uniform in size and free of fragmentsGrade II: Blastomeres that were uniform or slightly uneven in size with fragments < 20%Grade III: Blastomeres that were uniform or slightly uneven in size with fragments <20–50%Grade IV: Blastomeres that were uneven in size with fragments >50%

Grades I and II indicated high-quality embryos, and grades I, II, and III indicated transplantable embryos.2)Blastula evaluation criteria. Blastocysts could be classified as grades I–VI according to the degree of expansion and hatching, as follows:Grade I early blastula: The volume of the blastular cavity was smaller than half of the total volume of the blastocystGrade II blastula: The volume of the blastular cavity was larger than half of the total volume of the blastocystGrade III completely expanded blastula: The blastular cavity occupied the entire lumenGrade IV blastula after expansion: The volume of the blastular cavity was significantly larger than the early blastula, and the zona pellucida was thinnerGrade V incubating blastula: The blastula incubated from the rupture of the zona pellucidaGrade VI hatched blastula: the blastulae emerged completely from the zona pellucida.Grades III–VI blastulae were scored for inner cell mass (ICM) and trophoblast ectoderm cells.

The ICM scores were as follows:Grade A: A large number of cells, binding tightlyGrade B: Fewer cells, binding looselyGrade C: Very few cells

The trophoblast ectodermal cell scores were as follows:Grade A: A large number of cells distributed around the blastocystsGrade B: Fewer cells and relatively loose epithelial cellsGrade C: Very few cells

Blastocysts with a D5 score of ≥3AA, 3AB, 3BA, or 3BB or a D6–7 score of ≥4AA, 4AB, 4BA, or 4BB were identified as high-quality blastocysts.

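### The ectopic pregnancy rate is divided by a count that excludes ectopic pregnancies by definition, and the early abortion rate counts some losses that its denominator leaves out

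*Protocol article*

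**What the plan says.** All the relevant definitions stand in the protocol article under Secondary outcome measures.

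- **Clinical pregnancy.** The timing is "On day 35 after embryo transfer, a vaginal ultrasound showed", and the finding required is that "there was a gestational sac in the uterus with an embryo and fetal heart beat; this was determined as a clinical pregnancy". The section Frozen embryo transfer after thawing gives the same timing: "At 35 days after embryo transfer, B-scan ultrasonography was performed to check the clinical pregnancy status".
- **Ectopic rate.** "Ectopic pregnancy rate = the number of ectopic pregnancies/the total number of clinical pregnancies".
- **Early abortion rate.** "Early spontaneous abortion rate = the number of spontaneous abortions at a gestational age of <12 weeks/the total number of clinical pregnancies".
- **Earlier stage of pregnancy.** "Blood β-hCG and progesterone were measured 14 days after embryo transfer to evaluate whether a biochemical pregnancy was present".

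No wider definition of clinical pregnancy is given for the two rates. The clinical and ongoing pregnancy rates, by contrast, are taken over embryo transfer cycles. The Methods part of the abstract states: "The rates of embryo implantation, clinical pregnancy, and early spontaneous abortion were observed". It does not name ectopic pregnancy.

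**The concern.** A rate reported as a percentage, and compared between groups as one, needs every event to come from the set that is counted below the line. The ectopic rate fails this outright, because its denominator requires a sac in the uterus. The early abortion rate fails it in part, because a pregnancy can be lost before 12 weeks without ever having shown a heartbeat at day 35.

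Two things are at stake. First, the ectopic percentage does not estimate a probability. If it goes into the chi-square test that Statistical analysis methods prescribes for nominal variables, the non-event cell is wrong: subtracting ectopics from clinical pregnancies removes women who were never among them. Second, two analysts with the same data could report clearly different early abortion rates, depending on whether they count losses that precede the day-35 scan. Improving pregnancy outcomes is a stated aim of the trial, and early abortion is one of the outcomes named in the abstract.

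**Working it through.** The document states no figure for either rate, so there is nothing to reproduce. The check is one of set membership, followed by an illustration.

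**1. Ectopic rate.** The denominator requires a sac in the uterus; the numerator is pregnancies outside it. The two sets do not overlap, except for a heterotopic pregnancy, which is possible but rare when up to two embryos are transferred.

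**2. Gestational age at the day-35 scan.** Gestational age = 14 + embryo age + 35 days. The 14-day convention and an age of 3 days for cleavage-stage embryos are assumptions. Embryo scoring criteria covers blastocysts from D5 to D7.

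| Embryo age (days) | Gestational age at scan | Days left to 12 weeks (84 days) |
|---|---|---|
| 3 | 52 days = 7w3d | 32 |
| 5 | 54 days = 7w5d | 30 |
| 6 | 55 days = 7w6d | 29 |
| 7 | 56 days = 8w0d | 28 |

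**3. Early abortion rate.** Losses in those last 28 to 32 days come from pregnancies that had a heartbeat at the scan, so they are inside the denominator. Losses before day 35, and sacs without a heartbeat at day 35, are outside it. The numerator has an upper limit of 12 weeks and no lower limit, so its wording does not exclude them.

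**4. Illustration, all counts assumed.** Per group, let C be clinical pregnancies as defined, E ectopics, A0 intrauterine pregnancies lost before a day-35 heartbeat, and A1 losses after the heartbeat and before 12 weeks.

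| Quantity | Formula | C=20, E=2, A0=5, A1=2 | C=30, E=1, A0=3, A1=2 |
|---|---|---|---|
| Ectopic, as written | E/C | 2/20 = 10.0% | 1/30 = 3.3% |
| Ectopic, all pregnancies | E/(C+E+A0) | 2/27 = 7.4% | 1/34 = 2.9% |
| Abortion, all losses over C | (A0+A1)/C | 7/20 = 35.0% | 5/30 = 16.7% |
| Abortion, numerator restricted | A1/C | 2/20 = 10.0% | 2/30 = 6.7% |
| Abortion, denominator widened | (A0+A1)/(C+A0) | 7/25 = 28.0% | 5/33 = 15.2% |

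Between the all-losses reading and the restricted one, the abortion rate differs by a factor of 7/2 = 3.5 in the first example and 5/2 = 2.5 in the second.

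**5. No upper bound.** With C=2, E=3, A0=3 and A1=1, the ratios as written are 3/2 = 150% and 4/2 = 200%. These counts are extreme. They show only that the formulas are not bounded by 100%.

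**The case against.** **The abortion formula can be read sensibly.** The section separates biochemical from clinical pregnancy and expresses abortion per clinical pregnancy. A reader may take it to mean abortions among clinical pregnancies, which is a valid proportion. This stands as far as it goes: the text allows that reading but does not state it, and a sac without a heartbeat at the scan remains unplaced. For this rate the defect is an open lower limit. A reader might infer that the abortion denominator excludes its numerator altogether, as the ectopic one does. It does not, because losses between the day-35 heartbeat and 12 weeks are inside it.

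**A treatment that produces more pregnancies lowers any rate per pregnancy.** A reader might infer that the formulas as written would turn more clinical pregnancies into an apparent safety benefit. The documents do not support this as a defect of these formulas. With 2 ectopics and clinical pregnancies rising from 30 to 40, the stated ratio goes from 2/30 = 6.7% to 2/40 = 5.0%. With the ectopics added to the denominator it goes from 2/32 = 6.3% to 2/42 = 4.8%, almost the same fall. Nor does the section Safety evaluation indexes list either rate; it covers infection, bleeding duration, pain and allergic reactions. What remains is the general point that the number of pregnancies arises after randomisation, which is why counts per randomised woman are worth adding.

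**The rates have a low profile.** The section opens by naming endometrial thickness, menstrual volume and clinical pregnancy rate, and these two rates appear only as formulas at its end. Statistical analysis methods names no test for them specifically. Both points are fair and limit the weight of the finding.

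**Conclusion.** The point holds in full for the ectopic rate and in part for the early abortion rate. The ectopic formula is wrong as written: its denominator excludes its numerator by definition, and nothing elsewhere in the article widens that definition. The early abortion formula is underspecified: part of what its numerator admits cannot be in its denominator.

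Under the assumed counts, the ectopic rate shifts modestly (10.0% against 7.4%, or 3.3% against 2.9%), while the abortion rate varies 2.5- to 3.5-fold with the reading. These sizes rest on invented counts and are not estimates for this trial. The placing of the scan at about 7½ to 8 weeks rests on the assumed 14-day convention and the assumed day-3 age of cleavage embryos. The mismatch itself needs neither assumption beyond the scan falling before 12 weeks.

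The primary endpoint (adhesion repair) and the sample size do not depend on either rate. The definitions should still be corrected before analysis.

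**What to change.** Make each numerator a subset of its denominator.

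- **Ectopic pregnancy.** Use a denominator that contains ectopics: clinical pregnancies plus ectopics, all hCG-positive pregnancies, or embryo transfer cycles, as already used for the clinical and ongoing pregnancy rates.
- **Early spontaneous abortion.** Choose one of two forms and state it. Either restrict the numerator to losses before 12 weeks that follow a confirmed day-35 clinical pregnancy, and report sacs without a heartbeat and earlier losses on their own line. Or keep all such losses and widen the denominator to all ultrasound-confirmed intrauterine pregnancies. In either form, report biochemical losses separately; counting them as abortions would change the outcome.
- **Both events.** Also report counts per randomised woman by group, because any rate per pregnancy depends on how many pregnancies follow randomisation.

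The cost is wording. β-hCG at day 14 and the day-35 scan are already in the protocol, so no new procedure is needed. The widened abortion denominator does require a record of how each early pregnancy was confirmed, since day 35 is the only pregnancy scan that the article describes. The drawback is a slightly less direct comparison with published rates per clinical pregnancy.
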